CHW fidelity	Proportion of client messages replied to in an appropriate manner per CHW	Clinician review of eCHIS routine data throughout 2 years of study implementation	Not compared between arms

*GLMM* generalized linear mixed models, *RE* random effects, *SE* standard error

#### Service delivery and implementation outcomes

In addition to clinical outcomes, we will compare service delivery outcomes between arms as exploratory outcomes (Table 1). These outcomes are ascertained from eCHIS data and self-report questionnaires from all CHWs (*N* = 700). These include home visit coverage (defined as number of home visits performed by CHWs); perinatal clinic referrals (defined as number of clinic referrals logged by CHWs in eCHIS for clients who are pregnant or up to 3 months postpartum); and CHW and supervisor workload (defined as time on all work duties, based on self-report questionnaire).

Within the intervention arm, CHV-NEO acceptability, adoption and fidelity of use by CHWs and their supervisors is determined using questionnaires and eCHIS data. Acceptability is defined as perception by CHWs that CHV-NEO is agreeable or satisfactory, using the AIM scale in CHW self-report questionnaire [48]; adoption is defined as the proportion of client SMS replied to by CHWs at all based on eCHIS data; and fidelity is defined as the proportion of client SMS responded to by CHWs in an appropriate and timely fashion, ascertained through monthly structured review and scoring of a sample of SMS conversations by clinically trained study team members. Quantitative data from CHW and supervisor questionnaires as well as qualitative interviews with CHWs and supervisors are used to define CHW-, supervisor-, and facility-level drivers of acceptability, adoption, and fidelity.

### Participant timeline {13}

Peripartum women participants at control and intervention facilities complete questionnaires at enrollment into the study and at 6 weeks postpartum (Table 2). CHWs and supervisor participants complete questionnaires at study launch, 1 year after launch, and study close. CHW and supervisor qualitative interviews are conducted 1 year after launch and at study close.

**Table 2 Tab2:** CHV-NEO RCT participant schedule

Timepoint	Cluster randomization	Intervention deployment	Post-intervention deployment		RCT mid-point	RCT close-out
	***-t***_***2***_	***-t***_***1***_	**0**	***t***_***1***_	***t***_***2***_	***t***_***3***_
Peripartum women			Enrollment visit	6-week postpartum follow-up visit		
Allocation	*X*					
Eligibility screen			*X*			
Baseline ascertainment			*X*			
Clinical outcome ascertainment				*X*		
Closeout procedures				*X*		
CHWs and supervisors		Enrollment visit			1 year visit	Study close visit
Allocation	X					
Eligibility screen		X				
Informed consent		X				
Baseline ascertainment		X				
Mid-point qualitative and quantitative					X	
End-point qualitative and quantitative						X

Timepoints *-t*_*2,*_* -t*_*1,*_* t*_*2,*_* t*_*3*_ are on the trial implementation timeline, whereas timepoints 0 and *t*_*1*_ are on each participant’s pregnancy timeline

### Sample size {14}

Our study is powered for primary and secondary clinical outcomes. The cluster-randomized trial includes 20 facility clusters, 10 interventions, and 10 controls. For ascertainment of our primary outcome of neonatal mortality, we will abstract outcomes from eCHIS on 7200 pregnancies ending in live births across the clusters. With this sample size, assuming *α* = 0.05, two-sided tests, 10% attrition, a conservative coefficient of variation of 0.25, and assuming unequal cluster sizes with an average cluster size 360, we have 80% power to detect a difference in neonatal mortality of 21.0 vs. 10.3 per 1000 live births [43]. For ascertainment of secondary outcomes, we will enroll 2000 pregnant clients in the in-depth perinatal cohort. With this sample size, assuming *α* = 0.05, two-sided tests, 10% attrition, coefficient of variation of 0.25, and unequal cluster sizes (ranging between 80 and 120 per cluster), we have 80% power to detect a difference in early initiation of breastfeeding, thermal care, and cord care of 50% vs. 72%. We expect the outcomes of appropriate care-seeking and knowledge of danger signs to be correlated so we will correct these analyses for multiple comparisons. Assuming a Bonferroni-adjusted *α* = 0.025, we will have 80% power to detect a difference between arms of 2.0 vs. 2.4 danger signs named and 0.5 vs. 0.9 appropriate clinic visits attended in the first 6 weeks [6, 37, 49, 50].

Service delivery and implementation outcomes are ascertained among the in-depth perinatal cohort as well as all CHWs and supervisors providing services over the 2-year period (estimated sample size 700 CHWs and 40 supervisors). Quantitative and qualitative analyses of implementation outcomes are intended to be exploratory; no formal hypothesis testing will be performed. We expect sample sizes for qualitative interviews will be sufficient to reach theoretical saturation of themes [51].

### Recruitment {15}

#### Abstracted mortality cohort

Mortality is ascertained from the abstracted data from all perinatal clients enrolled in eCHIS in the study areas meeting the inclusion criteria. Clients are registered in eCHIS through CHWs’ routine home visit activities.

#### In-depth perinatal cohort

Participants in the in-depth perinatal cohort are recruited during ANC visits at the 20 randomized study facilities. Potential participants are approached by MCH facility staff and referred to the study staff at each clinic to obtain additional information. Study staff emphasize that participation is completely voluntary and will not affect their access to ANC, postnatal, or infant care services.

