### Trial design {8}

This study is a non-blinded cluster-randomized controlled superiority trial comparing two parallel arms (intervention vs. control). The study intervention is delivered by CHWs who are employed by Kisumu County and whose work takes place at the household and community level. Each CHW is assigned by the county to a community area for which they are responsible. Each CHW is affiliated with and supervised through a nearby assigned healthcare facility. The unit of randomization in our trial is the healthcare facility and the associated CHWs and community areas, referred to here as “facility clusters”. Twenty clusters were randomized to the intervention (eCHIS with integrated SMS, referred to as CHV-NEO) or the control (routine eCHIS without SMS) in a 1:1 allocation ratio (10 control clusters, 10 intervention clusters). All CHWs linked to each facility cluster provide the assigned intervention to their community-based clients.

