## Methods: participants, interventions, and outcomes

### Study setting {9}

This study takes place in community areas linked to 20 government healthcare facilities in Kisumu County, Kenya. Kenya has approximately 30,000 neonatal deaths each year [42], with a neonatal mortality rate of 21.0 per 1000 live births in Kisumu [43]; this is substantially higher than Sustainable Development Goal 3 of ≤ 12 neonatal deaths per 1000 live births by 2030 [44]. Facilities were selected to include a diversity of characteristics, including rural and urban location, a range of facility levels from health centers (level 3) to county hospitals (level 5), and patient volumes of 100–1000 monthly antenatal care visits.

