#### Pregnant women—in-depth cohort

Secondary clinical outcomes and implementation outcomes are ascertained among a nested cohort of women recruited by the study team when attending ANC visits at study facilities. Eligible participants for this cohort are pregnant (26–36 weeks gestation); registered as pregnant in eCHIS by a CHW linked to the study facility; age ≥ 14; receiving ANC at a study facility; able to read and respond to text messages in English, Kiswahili, or Luo or have someone in the household who can assist; have daily access to a mobile phone (own or shared) on Safaricom or Airtel networks; and plan to be in the area for at least 3 months postpartum. Participants who are enrolled in another research study or have previously been enrolled in CHV-NEO in a prior pregnancy are excluded.

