### Assignment of interventions: allocation

#### Sequence generation {16a}, concealment mechanism {16b}, and implementation {16c}

Facility-level cluster randomization was conducted using a restricted randomization approach. Facilities were stratified into eight groups of two to six facilities, based on similar characteristics that may influence outcomes of interest, including facility level, patient volume, rural/urban designation, and services offered. Randomization was conducted through an interactive event using an online visual simulation of randomization [52]. A representative from each facility “spun” an online “wheel” to determine their order of assignment within stratified groups and a second wheel to determine final assignment within the randomization stratum.

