### Assignment of interventions: blinding

#### Who will be blinded {17a}

This will be a non-blinded study. All facilities, trial participants, and analysts will have access to intervention assignment information. Study co-investigators will only review outcome data in aggregate across arms during the trial.

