#### Plans to promote participant retention and complete follow-up {18b}

A study staff member is stationed at each facility and is responsible for the recruitment and follow-up of participants. Participants who are 2 weeks late for their 6-week study visit are actively traced by phone call and home visit to maximize completeness of 6-week visit data. We successfully used this approach in previous RCTs [55]. Data from participants who discontinue the study will be included in the analysis up to the point of discontinuation.

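### Facility staff who know the allocation decide who is first approached for the in-depth cohort, and no arm-neutral rule is stated, so women put forward may differ by arm

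*Protocol article*

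**What the plan says.** - **Who makes the first approach.** Recruitment {15}, under the in-depth perinatal cohort: "Potential participants are approached by MCH facility staff and referred to the study staff at each clinic". The article states no consecutive, random or quota rule for whom they approach.
- **What they know.** Who will be blinded {17a}: "All facilities, trial participants, and analysts will have access to intervention assignment information". Sequence generation {16a} adds that a representative of each facility spun the wheels, including "a second wheel to determine final assignment within the randomization stratum".
- **Order of events.** Trial design {8} reports allocation as already done: "Twenty clusters were randomized to the intervention". Table 2 (Participant timeline {13}) places cluster randomisation before the women's enrolment visit.
- **Who screens.** Under informed consent {26a}, study staff explain the study, screen for eligibility and obtain consent. Section {18b} adds: "A study staff member is stationed at each facility and is responsible for the recruitment and follow-up of participants".
- **What depends on the cohort.** Outcomes {12} takes all secondary clinical outcomes from this cohort. Primary mortality comes from routine data on all eligible eCHIS clients (Recruitment {15}).
- **Stated safeguards.** Statistical methods {20a} specifies intention-to-treat analysis and adjustment for baseline characteristics that differ significantly between arms.

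**The concern.** Randomising clusters makes the clusters comparable. It does not make comparable the women later picked within them, if the person who picks knows the arm. Here the first gate to the cohort is staff of an allocated facility. Even with no intent to favour an arm, they may put forward different kinds of women: more motivated or better connected women where a new programme runs, or whoever is at hand where nothing has changed.

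Study staff cannot undo this, because they can screen only those who reach them. Intention-to-treat keeps each enrolled woman in her arm but has no bearing on who was enrolled. Adjustment triggered by a significant baseline difference misses imbalances that are unmeasured or fall short of significance. The covariates listed in section {18a} include education, income, parity, distance to clinic and self-efficacy, but no measure of phone or SMS engagement.

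At stake are breastfeeding initiation, cord care, thermal care, danger-sign knowledge and care-seeking. The trial claims power for these outcomes, and they carry its hypothesised mechanism.

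**Working it through.** **1. The plan's own figure.** Sample size {14} gives 80% power for 50% vs 72%, with 10 clusters per arm, about 100 women per cluster, 10% attrition, coefficient of variation k = 0.25 and two-sided alpha 0.05. With the Hayes–Bennett formula and m = 100 × 0.9 = 90:

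c = 1 + (1.96 + 0.84)² × [p0(1−p0)/m + p1(1−p1)/m + k²(p0² + p1²)] / (p0 − p1)²

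= 1 + 7.849 × [0.00278 + 0.00224 + 0.04803] / 0.0484 = 9.60 clusters per arm.

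Ten are planned, and power with ten is 81.7%. The stated power reproduces, so the point is about selection and not about sample size.

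**2. Pace of recruitment (derived, not stated).** 2000/20 = 100 women per facility. Trial status gives a start on 11 December 2023 and the end of data collection in December 2025, at most 24.7 months. Enrolment at 26–36 weeks with a 6-week postpartum visit takes 10–20 weeks of follow-up (assuming birth at 40 weeks).

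- No allowance for follow-up: 100/24.7 = 4.1 women per facility per month.
- 20 weeks' allowance: 100/20.1 = 5.0 per month.

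**3. Room for selection.** The planned eCHIS cohort is 7200, or 360 per cluster (about 15 per month over 24 months). The in-depth share is 2000/7200 = 28%. Some of the 360 would not meet the extra in-depth criteria, so the share of eligible women is higher. If only half were eligible (assumption), it would be 100/180 = 56%. Either way, a sizeable part of the pool is not enrolled.

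**4. Illustrative bias with no true effect.** Assumptions: engaged women have 1.3 times the chance of a good outcome and make up 50% of control enrolments and 60–70% of intervention enrolments.

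- 60%: (1 + 0.3 × 0.6)/(1 + 0.3 × 0.5) = 1.18/1.15 = 1.03
- 70%: (1 + 0.3 × 0.7)/(1 + 0.3 × 0.5) = 1.21/1.15 = 1.05

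On a 50% control rate this is 51.3% to 52.6%, a shift of 1.3 to 2.6 percentage points. Selection in the opposite direction gives 1.15/1.18 = 0.97 to 1.15/1.21 = 0.95.

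**5. Effect on false-positive risk.** With 50% in both arms, SE = √{[2 × 0.25/90 + 0.0625 × 2 × 0.25]/10} = 6.1 points.

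| Selection shift (assumed) | Two-sided false-positive risk |
|---|---|
| none | 5% |
| 1.3–2.6 points | about 5.5–7% |
| 5 points | about 12–13% |
| 10 points | about 35–38% |

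The first shifted row follows from step 4. The 5- and 10-point rows show sensitivity only; nothing in the documents points to shifts that large.

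**The case against.** **Eligibility is not left to facility staff.** Study staff screen and take consent, and the criteria are the same in both arms. This stands. A reader might infer that clinic nurses apply the judgement-based criteria, such as "able to read and respond to text messages in English, Kiswahili, or Luo or have someone in the household who can assist". The article does not say so: facility staff approach and refer, no more. What remains is that screening acts only on the women referred.

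**No SMS cue for clinic staff is documented.** A reader might also infer that nurses at intervention sites see who is already texting, and refer those women. SMS enrolment sits in the CHW home-visit workflow, and messages are read by CHWs and reviewed by their supervisors and the study team. Nothing gives clinic nurses that view. Messages also start at 28 weeks while eligibility starts at 26. This mechanism is conjecture, and the point does not depend on it.

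**The visit count exaggerates discretion.** Four to five women a month against "patient volumes of 100–1000 monthly antenatal care visits" gives 0.4–5% and suggests almost unlimited choice. That count includes repeat visits, other gestational ages and women not registered in eCHIS. The 28% share is the fairer figure.

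**The article is condensed.** The full protocol may contain an approach rule. That is possible, and the article does not say that staff pick among eligible women. But it does name an unblinded party as the first gate, and that stated step can be criticised as it stands.

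**The bias may be small.** On the assumptions above it is 1.3–2.6 points, against a design difference of 22 points and an SE of 6.1. This stands, and it limits the weight of the point.

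**Conclusion.** The point holds as a risk built into the stated recruitment step. Staff who know the arm make the first approach after allocation, the article states no rule common to both arms, and the stated safeguards cannot fully correct the result. It is not evidence that selection has differed by arm.

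It is confined to the questionnaire-based secondary and exploratory outcomes of the in-depth cohort. Size and direction cannot be known from the documents. The rate ratio of 1.03–1.05 under no effect rests wholly on the assumed 1.3-fold difference and the assumed 60–70% vs 50% mix. A shift of that order would not create the planned effect, but could tilt a borderline result. The change is worth making because it is cheap and removes a bias that analysis cannot remove.

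**What to change.** For remaining recruitment, revise the in-depth cohort paragraph under Recruitment {15}:

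1. In each recruitment session, take antenatal attendees at 26–36 weeks consecutively up to a session quota, by the same rule in both arms. The study staff member already stationed at the facility oversees this.
2. Facility staff only introduce the study to the women so identified.
3. Study staff apply the text-message criterion with one scripted question in both arms, without reference to current SMS use.
4. Keep a brief de-identified screening log (for example age, parity, gestational age, reason not enrolled) and compare it by arm.

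For women already enrolled, compare baseline characteristics by arm and report the comparison.

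Cost: a procedure amendment, which under section {25} goes to both ethics bodies before use, and slightly more screening time per session. No extra staff are needed. Women already recruited cannot be re-selected, so for them the comparison can describe an imbalance in measured characteristics but cannot remove it.

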#### CHWs and supervisors

CHWs and supervisors at all study facilities are recruited by study staff for participation in questionnaires through facility-wide group meetings or announcements from facility leadership at study facilities. CHWs or supervisors who join the study facility part-way through the study are recruited to complete subsequent rounds of data collection (1 year or trial close). It is emphasized that participation is completely voluntary and would not in any way affect their employment.

A subset of 50 CHWs and 10 supervisors at intervention sites are selected for individual interviews 1 year after the study trial launch and at trial close. Interview participants are selected based on exhibiting below-median vs. above-median fidelity to contrast the experiences of the two groups and identify constructs associated with variations in implementation. Selected individuals are contacted through facility leadership and invited to contact the study to learn more about participation. They and facility leadership are not be told why they were selected, to avoid any negative consequences from their workplace.

### Assignment of interventions: allocation

#### Sequence generation {16a}, concealment mechanism {16b}, and implementation {16c}

Facility-level cluster randomization was conducted using a restricted randomization approach. Facilities were stratified into eight groups of two to six facilities, based on similar characteristics that may influence outcomes of interest, including facility level, patient volume, rural/urban designation, and services offered. Randomization was conducted through an interactive event using an online visual simulation of randomization [52]. A representative from each facility “spun” an online “wheel” to determine their order of assignment within stratified groups and a second wheel to determine final assignment within the randomization stratum.

### Assignment of interventions: blinding

#### Who will be blinded {17a}

This will be a non-blinded study. All facilities, trial participants, and analysts will have access to intervention assignment information. Study co-investigators will only review outcome data in aggregate across arms during the trial.

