### Outcomes {12}

#### Clinical outcomes

Primary, secondary, and exploratory clinical outcomes are summarized in Table 1. The primary outcome is neonatal mortality, defined as the death of a live-born infant within 28 days of birth, based on routine data abstracted from eCHIS during the study period. Secondary outcomes are ascertained among the in-depth perinatal cohort who complete study questionnaires. Secondary outcomes were selected based on the intervention’s hypothesized mechanism of action (Fig. 2) and their importance as intermediate outcomes in neonatal survival. These include initiation of breastfeeding within the first hour of life (ascertained by maternal self-report at the 6-week postpartum study visit); application of substances to cord (ascertained by maternal self-report at the 6-week visit); maternal knowledge of neonatal danger signs (defined as the number of the eight neonatal danger signs correctly named at the 6-week visit); and appropriate care seeking (defined as the proportion of illness episodes with danger signs where the infant attended the clinic, based on maternal self-report at the 6-week visit). Exploratory clinical outcomes include mothers’ identification of danger signs in their infants (defined as the proportion of all infants whose mothers report they ever exhibited a danger sign at the 6-week visit); infant hospital admissions (based on maternal self-report); and neonatal care delays (defined as the proportion of neonatal deaths attributable to each delay in the three delays model, based on review of adverse event reports by nurses and physicians on the study team).

**Table 1 Tab1:** Trial outcomes

Outcome	Indicator	Source and timing	Statistical analysis
Primary clinical outcome			
Neonatal mortality	Death during the first 28 days of life	eCHIS routine data throughout 2 years of study implementation	GLMM (RE by facility and CHW) with Poisson link and survival time as offset
Secondary clinical outcomes			
Initiation of early breastfeeding	Breastfed in the first hour of life	Questionnaire at 6-week visit	GLMM (RE by facility and CHW) with Poisson link and robust SE
Appropriate cord care	Application of nothing or chlorhexidine to umbilical cord	Questionnaire at 6-week visit	GLMM (RE by facility and CHW) with Poisson link and robust SE
Appropriate thermal care	No bath in the first 24 h of life	Questionnaire at 6-week visit	GLMM (RE by facility and CHW) with Poisson link and robust SE

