### Statistical methods

#### Statistical methods for primary and secondary outcomes {20a}

Statistical analysis approaches for each outcome are summarized in Table 1. Analysis of primary and secondary outcomes will be by intention-to-treat. If participants relocate between facilities in different intervention arms during the course of the study, the original assignment is used in the analysis. For analyses that include random effects at the CHW level, if a participant’s assigned CHW changes, their data is analyzed under the CHW under whose care they are for the longest proportion of follow-up time preceding outcome ascertainment. Analyses will be adjusted for any baseline characteristics that differ significantly between study arms.

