#### Methods in the analysis to handle protocol non-adherence and any statistical methods to handle missing data {20c}

Based on the Mobile WACh NEO RCT [41], we expect a 10% loss to follow-up between enrollment and the 6-week study visit. We anticipate that women who are lost to follow-up are more likely to be disengaged from care and have experienced adverse outcomes. We also anticipate missingness may differ by arm, with the intervention arm having higher retention. A secondary analysis of mortality will be performed in which missing mortality at 28 days will be imputed using multiple imputations by chained equations (MICE).

To explore any dose–response effects associated with variation in the fidelity of intervention delivery, we will conduct an exploratory analysis comparing primary and secondary outcomes between participants who received low vs. high fidelity of the intervention, defined based on the number of automated and CHW messages received. Propensity score matching will be used to control for confounding by participant or CHW characteristics.

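### Analysts know the allocation although they could be masked, and the primary model's covariates are to be picked from observed between-arm differences

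*Protocol article*

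**What the plan says.** All places are in the protocol article.

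- **Who will be blinded {17a}.** "All facilities, trial participants, and analysts will have access to intervention assignment information". The one restriction is on a different group: "Study co-investigators will only review outcome data in aggregate across arms during the trial". Analysts are not covered by it.
- **Statistical methods {20a}**, which covers primary and secondary outcomes. "Analyses will be adjusted for any baseline characteristics that differ significantly between study arms".
- **Already fixed in the same section.** Analysis is by intention to treat. For women who move between arms, "the original assignment is used in the analysis". If a woman's CHW changes, "their data is analyzed under the CHW under whose care they are for the longest proportion of follow-up time preceding outcome ascertainment".
- **Clinical outcomes and Table 1.** Neonatal mortality is "defined as the death of a live-born infant within 28 days of birth, based on routine data abstracted from eCHIS during the study period". The model is a Poisson mixed model with facility and CHW random effects and a survival-time offset.
- **Eligibility criteria.** Entry to the mortality cohort depends on eCHIS registration of the pregnancy by 36 weeks by a study-linked CHW.
- **Missing data {20c}.** "A secondary analysis of mortality will be performed in which missing mortality at 28 days will be imputed". Imputation is thus kept out of the primary analysis.

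**The concern.** Analyst masking is one of the few protections against bias still available in a trial whose providers and participants must know their arm. The protocol addresses it explicitly and gives it up. It does recognise the risk for co-investigators, who see only pooled outcomes while the trial runs.

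This would matter little if nothing in the primary analysis waited on data by arm, but the covariate set does. With 20 randomized facilities some chance imbalance is to be expected, and the covariates that enter the model can move the estimated mortality ratio. An analyst who applies a significance rule with the arm labels in hand, and with outcomes available by the end of the trial, has room to influence the estimate without intending to. The same people turn routine records into the analysis dataset while knowing the arm. The trial is meant to inform national scale-up, so the mortality result should be free of that doubt.

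**Working it through.** **1. The plan's own figure.** Inputs from Sample size {14}: p0 = 0.0210, p1 = 0.0103, 10 clusters per arm, mean cluster size 360, 10% attrition (m = 324), between-cluster coefficient of variation k = 0.25, two-sided α = 0.05, 80% power. Hayes–Bennett formula for proportions, assuming equal cluster sizes:

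c = 1 + (1.96 + 0.84)² × V / (p0 − p1)², with V = p0(1−p0)/m + p1(1−p1)/m + k²(p0² + p1²)

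- V = 0.00006345 + 0.00003146 + 0.00003419 = 0.00012911
- (p0 − p1)² = 0.00011449
- c = 1 + 7.849 × 0.00012911 / 0.00011449 = 9.85, so 10 clusters per arm

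With the one-cluster correction, z = 0.0107 / √(V/9) = 2.825, and power is Φ(2.825 − 1.96), about 0.806. The stated 80% is reproduced.

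**2. Expected deaths.** 3,600 per arm less 10% is 3,240. Then 3,240 × 0.0210 = 68.0 and 3,240 × 0.0103 = 33.4, about 101 in all (75.6 + 37.1, about 113, without attrition).

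**3. How far the planned result lies from the boundary.** The same variance is used at the observed proportions, divided by 9 (with the cluster correction) or 10 (without), with a normal reference:

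| Deaths, control vs intervention | p, divisor 9 | p, divisor 10 |
|---|---|---|
| 68 vs 33 | 0.0043 | 0.0026 |
| 68 vs 42 | 0.043 | 0.033 |
| 68 vs 43 | 0.052 | 0.041 |
| 68 vs 44 | 0.064 | 0.051 |

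From 68 vs 33, significance is lost after 10 to 11 added intervention deaths. It is also lost after 13 to 15 fewer control deaths, or 6 to 7 changes of each kind together. The ranges span the divisor, a t reference on 18 df with divisor 10, and the log-ratio form below.

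**4. The same distance for covariate adjustment.** On the log rate-ratio scale, SE = √(1/68 + 1/33 + 2 × 0.25²/10) = √0.0575 = 0.240. The unadjusted ratio is 33/68 = 0.485, with log −0.723. The boundary is at −1.96 × 0.240 = −0.470, a ratio of 0.625. With the SE held fixed, adjustment would have to move the ratio from 0.485 to about 0.625.

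**5. Near the boundary.** On this scale 62 vs 39 gives p = 0.047 and 61 vs 40 gives p = 0.069, so one paired change is enough.

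**6. How often a result lies that close.** In 40,000 simulated gamma-binomial trials at the design rates with k = 0.25, adding or removing up to three deaths in one arm reversed the verdict in 10.2 to 13.7% of trials with 3,240 per arm, and in 8.6 to 11.3% with 3,600.

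**7. What these numbers are not.** They show how sensitive the verdict is. They do not estimate bias. The article gives no covariate–mortality association and no count of records that call for judgement, so the actual shift cannot be calculated.

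**The case against.** The strongest reply is that nearly everything is already settled. Gestation at registration, the 28-day live-born definition, intention to treat, women who move, CHW attribution, the model and the place of imputation are all written down. Deaths are extracted directly from the eCHIS server. Clinician review of deaths serves the exploratory care-delay outcome only, and no text gives analysts a role in adjudicating primary-outcome deaths. Duplicate handling, cleaning and lock rules commonly sit in an analysis plan or full protocol, which are not shown, so their absence is no fault here. All of this stands.

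A reader might infer that unmasked analysts will decide which deaths count, so that a few of about 100 can decide the trial. The documents do not support that. The one choice shown to be open concerns covariates, and at the planned effect about 10 deaths would have to change. Any trial near p = 0.05 can be tipped by one or two events.

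A reader might also infer that covariates will be chosen for their effect on the result. The rule refers to baseline differences only, and an analysis plan may fix the candidates and the test.

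It can also be said that the article is open about a declared non-blinded design and does not contradict itself. That is true. But the protocol states analyst access as a decision, and it states a covariate rule that cannot be applied without arm labels. Neither is an omission that another document would fill.

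**Conclusion.** The concern holds in a limited form. Analysts are given the allocation without need, and the covariates of the primary model depend on between-arm comparisons made by people who know the arm. The consequence is small at the planned effect (p about 0.004 with the cluster correction) and material only near the boundary, which under the design alternative means roughly 9 to 14% of trials if up to three deaths in one arm are in play.

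These sizes rest on the article's rates, 10% attrition or none, k = 0.25 and equal cluster sizes, since the spread of cluster sizes in the mortality cohort is not given. The change is worth making because it is cheap. The plan as written does not invalidate the trial.

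**What to change.** Make two changes together, because a covariate list cannot be locked under masking while it is selected by differences between arms.

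1. **Who will be blinded {17a}.** State that analysts prepare the mortality dataset and the primary-model code on an export with arm removed, facility codes scrambled and SMS fields withheld (SMS records would reveal the intervention arm). Attach arm only after dataset and code are locked. Code and covariate list should be locked before the interim mortality analysis, since arm is needed for it.
2. **Statistical methods {20a}.** Replace the significance-based rule with a covariate list fixed in advance, for example the factors used to stratify randomization: facility level, patient volume, rural or urban setting, and services offered. With 20 clusters the list should be short. Baseline differences can still be tabulated descriptively.

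**Cost.** One recoding step at export, which the existing data manager could do, and later access to SMS fields for the fidelity and dose–response analyses, which come after the primary analysis anyway. Sample size and data collection are unchanged.
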